## Analysis

### Outcome definitions

#### Primary outcome

**Table Tabb:** 

Outcome	Definition	Time frame
Stroke and TIA	The occurrence of stroke, including TIA. Both are considered clinical diagnoses constituted by acute focal or global neurological symptoms brought on by thromboembolism or hemorrhage in the brain. The event is defined as a TIA if symptoms last less than 24 h. If patients with a stroke diagnosis receive thrombolytic treatment leading to complete symptom remission, the event is considered a stroke. If patients are diagnosed with amaurosis fugax, the event will be regarded as a TIA. If patients are diagnosed with retinal artery occlusion, the event will be considered a stroke. The stroke subtypes will not be discerned in the primary outcome analyses, i.e., both ischemic and hemorrhagic types are included. The first adjudicated primary outcome is included, while later occurring events are disregarded.	2 years from index surgery

#### Secondary outcomes

**Table Tabc:** 

Outcome	Definition	Time frame
Stroke, TIA, and SCI (composite)	Composite outcomes of stroke, including TIA and SCI. Stroke and TIA are defined as for the primary outcome and are included regardless of the results of computed tomography (CT) or magnetic resonance imaging (MRI) scans. SCI entails a fresh lesion on a CT or MRI scan without concomitant symptoms or a new-onset lesion of an older date in patients with recurring scans. The stroke subtypes will not be discerned in the primary outcome analyses, i.e., both ischemic and hemorrhagic types are included.	2 years from index surgery
Ischemic stroke, including TIA	The diagnosis of stroke or TIA is defined in the primary outcome, but where CT or MRI scan(s) show ischemic lesion congruent with symptoms.	2 years from index surgery
All-cause mortality and stroke (composite)	Death of any cause or the diagnosis of stroke. The diagnosis of stroke is defined as the primary outcome. There is no discerning between stroke subtypes. TIA is not included in this outcome.	2 years from index surgery

The outcomes will be analyzed in the order they are reported

Neurological outcomes will be adjudicated by two neurologists. If a neurological event occurs, the site’s study investigators will draw a report from the patient’s medical chart. The report includes data on patient symptoms, clinical and paraclinical examinations performed, cerebral CT or MRI scan descriptions (as described by neurological radiologists), and any medication initiated during admission. The reports will be anonymized, and the neurologists will be blinded to study allocation. The events will be assigned by consensus of the two neurologists if there are discrepancies in the adjudications.

Stroke subtypes will be differentiated by cerebral CT or MRI scans showing lesions congruent with the symptoms. In the case of hemorrhagic transformation of an ischemic stroke, the event will be considered an ischemic stroke. Moreover, retinal artery occlusions will also be considered an ischemic stroke event.

SCI is a lesion on cerebral CT or MRI scans without neurological symptoms. The SCI may either be fresh ischemic, i.e., showing hyper-intensity on diffusion-weighted imaging (DWI) and apparent diffusion coefficient (ADC) hypo-intensity, or a new-onset non-fresh lesion in a patient with one or more previous scans.

No study-specific cerebral CT or MRI scans will be performed; accordingly, only scans performed in a clinical setting will be considered.

#### Other outcomes

**Table Tabd:** 

Outcome	Definition	Time frame
Systemic embolism	A clinical diagnosis of an acute non-cerebral artery occlusion	2 years from index surgery
AF occurrence or recurrence	The recurrence or occurrence of AF during follow-up for patients with sinus rhythm at discharge after index surgery	2 years from index surgery
All-cause mortality	Death from any cause	2 years from index surgery

New-onset AF occurring from index surgery until discharge will be considered “postoperative AF”. If patients are discharged in sinus rhythm and have an occurrence or recurrence of AF within 3 months from index surgery, the episode will be defined as an “early” AF occurrence or recurrence, while AF occurrence after 3 months will be defined as “late”. Only the first incidence of postoperative AF and the first incidence of occurrence or recurrence of AF will be registered. No study-specific continuous cardiac rhythm monitoring will be performed during admission; hence, the evaluation will be based on AF detection in the clinical setting and rely on registration in the electronic medical chart. Any available electrocardiogram (ECG) will be used to verify AF. Continuous cardiac rhythm monitoring after discharge is planned at selected sites for a subgroup of patients with postoperative AF discharged in sinus rhythm and without recurrence of AF in the subsequent years. If more than 30 s of AF is seen on the monitoring or a 12-lead ECG, patients will be considered to have AF recurrence.

### Analysis methods

The respective investigators gather data from each site, and primary and secondary analyses will be performed centrally.

The primary analyses rely on time-to-event (survival) statistics.

The possible events are as follows:I.Primary outcome occurrenceII.DeathIII.Withdrawal of consentIV.Last contact (loss to follow-up)V.Trial end*

*The time frame is at least 2 years from index surgery; thus, follow-up continues for all patients until the last enrolled patient has been followed for 2 years.

The time between randomization and event (I–V) is the exposure time.

The primary analyses will be based on the ITT principle, i.e., it includes all randomized patients with an available baseline assessment independently of the performed surgery.

PP analyses will serve as sensitivity analyses.

#### Analyses of the primary outcome

Cumulative incidence (Aalen-Johansen) plots will display results of the primary outcome with death as a competing risk. Gray’s test for differences between cumulative incidence rates will be used to assess statistical significance.

As the primary outcome will be examined in a competing risk setting, cause-specific Cox regression is used to quantify the difference in risk between allocation groups. The main covariate is randomization (LAA closure vs. open LAA). The analysis will be adjusted for the stratification factors before randomization, i.e., site, surgery type, and OAC therapy. The results will be presented as hazard ratio (HR) with 95% confidence intervals.

The null hypothesis is that there is no difference between the cumulative incidence rates of the two treatment groups.

The decision rule for the hazard ratio is as follows:

VI.Superiority of LAA closure will be accepted if the estimated HR is < 1 and the 95% confidence interval (CI) does not include 1VII.Superiority of open LAA will be accepted if the estimated HR is > 1 and the 95% CI does not include 1VIII.No superiority will be accepted if the 95% CI contains 1

Proportional hazard assumptions for the Cox regression models will be tested by interaction terms with time on study, weighted Schoenfeld, and cumulative Martingale residuals. If non-proportionality is detected for covariables used for adjustment (site, surgery type, and OAC therapy), these factors will be included as stratification variables. If non-proportionality is detected for the primary exposure (randomization), time-varying hazard ratios with 95% confidence intervals will be used to assess the differential effect of randomization as a function of time-on study.

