**Methods:**

The study is designed as a randomized, open-label, blinded outcome assessor, multicenter trial of adult patients undergoing first-time elective open-heart surgery. Patients with and without AF and any CHA_2_DS_2_-VASc score will be enrolled. The primary exclusion criteria are planned LAA closure, planned AF ablation, or ongoing endocarditis. Before randomization, a three-step stratification process will sort patients by site, surgery type, and preoperative or expected oral anticoagulation treatment. Patients will undergo balanced randomization (1:1) to LAA closure on top of the planned cardiac surgery or standard care. Block sizes vary from 8 to 16. Neurologists blinded to randomization will adjudicate the primary outcome of stroke, including transient ischemic attack (TIA). The secondary outcomes include a composite outcome of stroke, including TIA, and silent cerebral infarcts, an outcome of ischemic stroke, including TIA, and a composite outcome of stroke and all-cause mortality. LAA closure is expected to provide a 60% relative risk reduction. In total, 1500 patients will be randomized and followed for 2 years.

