### Randomization and stratification

Before randomization, a three-step stratification is performed. The first step is “site,” the second is “surgery type,” and the third is “use of oral anticoagulant (OAC)” (see the table below).

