### Sample size

Based on previous studies, estimated event rates are 1.2% vs. 3.0% per year for patients with and without LAA closure, respectively [8, 9, 11, 16, 18, 19]. A total of 1302 patients need to be included if they are randomized 1:1, followed for 2 years, and a significance level of 0.05 and 90% power is to be achieved. With these numbers, 16 primary events are expected for patients with LAA closure and 39 for patients with an open LAA. The trial will enroll 1500 patients to account for deviations in treatment allocation and death. Please see the trial protocol for more details [20].

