## Statistical principles

### Confidence intervals and *P* values

A significance level of 5% and a confidence interval of 95% will be applied. No multiplicity adjustment is planned; consequently, findings in secondary outcomes are considered exploratory. Only two-sided significance tests will be used.

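### Gray's test, named to assess significance of the primary outcome, is stated without the strata used at randomization, while the Cox model is adjusted for them

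*SAP article*

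**What the plan says.** SAP article, Randomization and stratification: "Before randomization, a three-step stratification is performed". The steps are site (4 levels), surgery type (3) and OAC (2), with 1:1 allocation in each stratum and block sizes of 8 to 16.

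SAP article, Analyses of the primary outcome:
- Gray's test for differences between "cumulative incidence rates will be used to assess statistical significance". No strata are mentioned.
- A cause-specific Cox regression then quantifies the difference. The sentence on adjusting for site, surgery type and OAC belongs to this model.
- The three superiority statements rest on the 95% confidence interval of the Cox HR.
- If a proportional-hazards check flags an adjustment factor, "these factors will be included as stratification variables".

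SAP article, Sample size and Confidence intervals and P values: "a significance level of 0.05 and 90% power is to be achieved"; "Only two-sided significance tests will be used".

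**The concern.** When randomization is stratified by factors that predict stroke, the arms are balanced on them by design. A test that ignores the strata still counts the between-stratum variation as noise. Its variance is then a little too large, its type I error falls a little below 5%, and it loses some power.

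The plan also reports a p-value and an HR interval that treat the strata differently, and either could be read as the verdict. With about 55 events a result near the boundary is plausible, and a p-value on one side with an interval on the other would be awkward to report. Part of that disagreement is avoidable.

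**Working it through.** **1. The plan's own figure.** Inputs from Sample size: "estimated event rates are 1.2% vs. 3.0% per year for patients with and without LAA closure", so p1 = 0.024 and p2 = 0.060 over 2 years, with mean 0.042; two-sided 5%, 90% power. Pooled-variance formula for two proportions:

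n per arm = [1.960·√(2·0.042·0.958) + 1.282·√(0.024·0.976 + 0.060·0.940)]² / 0.036² = (0.556 + 0.362)² / 0.001296 ≈ 650.4, rounded up to 651.

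The total is 2 × 651 = 1302, as stated. Expected events are 651 × 0.024 + 651 × 0.060 = 15.6 + 39.1 ≈ 55, also as stated. This calculation has no strata in it.

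**2. Number of strata.** 4 × 3 × 2 = 24 cells, so 55 / 24 ≈ 2.3 events per cell on average.

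**3. Simulation of the test.** n = 1302, 24 cells, permuted blocks of 8 to 16, 2 years of follow-up, 4000 runs per setting. Gray's test was approximated by a log-rank test that keeps deaths in the risk set.

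Assumptions not in the document: shares of 35/35/20/10% (sites), 45/15/40% (surgery types) and 30/70% (OAC); 2% yearly mortality; and the strength of the strata. In the moderate setting the log-hazard range between extreme levels is 1.0 for site, 1.1 for surgery type and 0.8 for OAC, that is HRs of e^1.0 = 2.7, e^1.1 = 3.0 and e^0.8 = 2.2. The strong setting doubles these: e^2.0 = 7.4, e^2.2 = 9.0 and e^1.6 = 5.0.

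| Rejection rate, unstratified → stratified | no effect | moderate | strong |
|---|---|---|---|
| HR 0.4 | 89.6 → 89.6% | 88.4 → 88.7% | 84.9 → 87.4% |
| HR 0.5 | 72.8 → 72.9% | 71.9 → 72.2% | 64.0 → 68.5% |
| HR 1 (type I error) | 4.7 → 4.7% | 4.9 → 5.2% | 3.8 → 4.8% |

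The Monte Carlo error of a type I rate is √(0.05·0.95/4000) ≈ 0.34 points. The 0 to 0.3 point differences therefore cannot be told from zero. The 3.8% can be told from 5%: (5.0 − 3.8)/0.34 ≈ 3.5 standard errors.

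A separate simulation with 1500 patients and stratum effects of up to HR 2.9 agrees: type I error 4.7% unstratified and 5.0% stratified, and power gains of 0.6 points (HR 0.5) to 1.0 point (HR 0.6).

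**4. Disagreement between test and interval.** In the 1500-patient simulation the two gave different verdicts in 1.0%, 2.1% and 4.2% of trials across three settings. With both the test and the Cox model stratified, this fell to 0.2%, 0.9% and 1.5%. It does not reach zero, because Gray's test compares cumulative incidence and the Cox model compares cause-specific hazards.

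These figures do not describe stratifying Gray's test alone. When only the test is stratified and the Cox model keeps its covariates, disagreement falls clearly only with strong strata. With null or moderate strata it stays about the same.

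**5. The Cox model** (1600 runs per setting). Stratifying on all 24 cells instead of using covariates changed power at HR 0.4 from 89.6% to 89.2% (no effect) and from 88.8% to 88.5% (moderate). With two very small sites the changes were 88.3% to 88.0% and 87.3% to 86.8%. In the separate simulation the standard error of the log HR rose by 0.2% to 0.9%.

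The plan's switching rule was read as one 5% test per factor. With truly proportional hazards it changed the model in 13–16% of runs, close to 1 − 0.95³ = 14%. Type I error stayed at 4.4–4.9%.

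**The case against.** The strongest reply is that little is at stake. An unstratified test after stratified randomization is valid and errs on the safe side. The written superiority rule uses the Cox interval, and that model already adjusts for all three factors. The article does not call Gray's test unstratified; that is read from its silence. At the design effect ("LAA closure is expected to provide a 60% relative risk reduction") the gain is close to nil unless the strata are very prognostic. All of this stands, and it keeps the point small. The silence still matters, because the same section assigns the adjustment to one method and not to the one named for significance.

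A reader might infer that the Cox model is also at fault because its form is settled after looking at the data. The document does not support that as an error. The switch is written in advance, concerns only adjustment factors, does not depend on the treatment estimate, and left type I error intact. It lacks a threshold for detecting non-proportionality, which is a matter of wording. Covariates against strata is a trade-off between two accepted methods, and 24-cell stratification is slightly less precise, so it is not free.

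A reader might also assume that risk sets within strata stay large and balanced. The document gives no stratum shares. Under the shares assumed above, the smallest cell holds 1500 × 0.10 × 0.15 × 0.30 = 6.75, about 7 patients, fewer than the smallest block of 8. With a 4% site it holds 1500 × 0.04 × 0.15 × 0.30 = 2.7, about 3. Stratifying Gray's test still lost no power in the settings simulated, but large cells are not the reason.

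**Conclusion.** The point holds for Gray's test and is minor. As written, the test named for significance does not use the randomization strata, while the HR interval does. The consequence is some lost power and some avoidable disagreement, not false positives. At HR 0.4 stratifying gains 0 to 0.3 points with null to moderate strata and 84.9% to 87.4%, about 2.5 points, with strong ones. At HR 0.5 with strong strata it gains about 4.5 points. The strong setting assumes HRs of 5 to 9 between extreme levels, so the lower end is the more likely one. The sizes rest on assumed stratum shares, mortality and prognostic strength, and on an approximation to Gray's test.

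Stratifying reduces disagreement with the Cox interval but does not remove it, and most of the measured reduction needs both analyses stratified. Which of the two decides superiority is a separate question that this change does not settle.

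**What to change.** Add to Analyses of the primary outcome: Gray's test will be stratified by site, surgery type and OAC as recorded at randomization. This costs one sentence and one argument in the software call, and it lost no power in any setting simulated.

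Leave the Cox model's covariate adjustment as it is. Stratifying it by the same three factors from the outset is optional. It would bring test and interval closer and make the switch for these factors unnecessary. It costs a negligible amount of precision (0.2% to 0.9% in standard error) and gives up the HRs for the three factors, which the plan uses only for adjustment. The proportional-hazards check on the treatment term is unaffected.

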### Baseline patient characteristics

The following baseline patient characteristics will be presented:

I.Demographics: age and sexII.Measurements:◦ Optional: height, weight, blood pressure, left ventricular ejection fraction, and estimated glomerular filtration rateIII.Comorbidities: prior stroke, TIA, AF, or atrial flutter◦ Optional: ischemic heart disease, peripheral artery disease, cardiac valve disease, congestive heart failure, pacemaker or implantable cardioverter defibrillator implantation, hypertension, chronic obstructive/restrictive pulmonary disease, diabetes mellitus, chronic kidney disease, autoimmune disease, active cancerIV.Medications: any heart rhythm or frequency modulators, anticoagulation, or antiplatelet therapyV.Prior brain scans: any brain scan performed before study enrolment, including findings

Continuous variables will be summarized as mean (standard deviation) or median (interquartile range), while categorical variables are summarized as frequencies (percentages).

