#### Subgroup analyses

Subgroup analyses will investigate the interaction of outcomes and key stroke risk factors. Predefined analyses are as follows:I.Prior stroke, including TIAII.Prior AFIII.Recurrent AFIV.Pre-operative CHA_2_DS_2_-VASc scoreV.Preoperative and postoperative OACVI.Preoperative and postoperative antiplatelet therapy

The interaction terms will be added to the Cox models described in the primary and secondary outcome analyses above. A significant subgroup effect will be considered if the *p*-value ≤ 0.05. Each interaction term’s HR and 95% CI will be presented in a forest plot.

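### The primary Cox model leaves out age, prior stroke/TIA and prior AF; it is valid, but prespecifying these covariates would be a small, cheap improvement

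*SAP article*

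**What the plan says.** In the SAP article, section Analyses of the primary outcome, the adjustment set of the cause-specific Cox model is fixed: "The analysis will be adjusted for the stratification factors before randomization, i.e., site, surgery type, and OAC therapy". The same section accepts superiority when the 95% confidence interval of the hazard ratio excludes 1. It also names Gray's test, which takes no covariates, for statistical significance.

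The section Baseline patient characteristics lists age and sex, and then "Comorbidities: prior stroke, TIA, AF, or atrial flutter". These entries stand outside the lists marked optional.

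The section Subgroup analyses begins: "Subgroup analyses will investigate the interaction of outcomes and key stroke risk factors". Its list includes prior stroke with TIA, prior AF, the preoperative CHA2DS2-VASc score and OAC. Age is not listed on its own and enters only through the score.

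The section Sensitivity analyses offers per-protocol and complete-case analyses. It has no analysis with further covariates.

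**The concern.** The trial enrols patients with and without AF and at any CHA2DS2-VASc score, so baseline stroke risk differs widely by design. Randomization is stratified by site, surgery type and OAC, but not by age, prior stroke/TIA or prior AF. The Cox model follows the same three factors.

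Two things are at stake:

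- **Power.** In a Cox model, leaving out strong prognostic covariates pulls the estimated treatment effect slightly towards 1. With about 55 events, the confidence limit near 1 may be close.
- **Prespecification.** If the arms happen to differ in prior stroke or AF, any analysis adjusted for that difference would be post hoc. The article says that it aims to limit reporting bias.

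**Working it through.** **1. The plan's own figure.** Inputs from the section Sample size: "estimated event rates are 1.2% vs. 3.0% per year for patients with and without LAA closure, respectively", 2 years, 90% power and a significance level of 0.05. The section on confidence intervals adds: "Only two-sided significance tests will be used". The two-year risks are 2 × 1.2% = 2.4% and 2 × 3.0% = 6.0%, with mean 4.2%. The two-proportion formula with pooled variance gives, per arm,

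n = [1.960 × √(2 × 0.042 × 0.958) + 1.2816 × √(0.024 × 0.976 + 0.06 × 0.94)]² / 0.036² = (0.556 + 0.362)² / 0.001296 ≈ 650.4, rounded up to 651.

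The total is 1302, as stated. Expected events are 651 × 0.024 = 15.6 and 651 × 0.06 = 39.1, which matches "16 primary events are expected for patients with LAA closure and 39 for patients with an open LAA".

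**2. Parameters.** Site (4 levels), surgery type (3) and OAC (2) use 3 + 2 + 1 = 6 parameters, and treatment makes 7. Three covariates more make 10. Events per parameter fall from 55/7 = 7.9 to 55/10 = 5.5.

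**3. Power, present model against the model with three more covariates.** The article gives no prevalence and no prognostic hazard ratio for these factors, so all inputs on them are assumptions.

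*Simulation A:* 1500 patients, 2 years, open-arm rate 3% per year, 12,000 trials per setting, counting rejections in favour of closure. Moderate setting: AF in 20% (HR 2), prior stroke/TIA in 10% (HR 2.5), age HR 1.5 per SD. Strong setting: the log hazard ratios multiplied by 1.5, so HRs of about 2.8, 4.0 and 1.8.

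| True HR | Moderate | Strong |
|---|---|---|
| 0.4 | 91.9% to 92.3% (+0.4) | 90.5% to 91.9% (+1.4) |
| 0.5 | 76.3% to 77.0% (+0.7) | 74.1% to 76.0% (+1.9) |
| 0.6 | 53.0% to 53.9% (+0.9) | 50.7% to 53.4% (+2.7) |

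The paired standard error of each difference is 0.1 to 0.3 points. Two-sided type I error is 4.8%.

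*Simulation B:* 1302 patients, 1500 trials per setting, prior stroke in 10%, AF in 15%, OAC in 85% of patients with AF and 12% without, death 2.5% per year.

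| True HR | Assumed HRs (stroke / age per SD / AF) | Power |
|---|---|---|
| 0.40 | 1 / 1 / 1 | 87.8% to 88.1% (+0.3) |
| 0.40 | 2 / 1.3 / 1.5 | 88.8% to 88.3% (−0.5) |
| 0.40 | 2.5 / 1.5 / 1.8 | 86.0% to 86.3% (+0.3) |
| 0.40 | 4 / 2 / 2.5 | 83.9% to 86.2% (+2.3) |
| 0.55 | 2.5 / 1.5 / 1.8 | 57.9% to 58.2% (+0.3) |
| 0.55 | 4 / 2 / 2.5 | 55.6% to 59.0% (+3.4) |

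Each power figure has a simulation error of about 0.9 points at HR 0.40 and 1.3 at HR 0.55. Type I error is 4.4% with the present model and 4.3% with the larger one. The gain comes from the estimate, not from its standard error: in the strong setting at HR 0.40 the mean estimate moves from 0.407 to 0.392, while the standard error of the log HR goes from 0.318 to 0.320.

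*Simulation C:* 1500 patients, with OAC correlated with AF. Gains are 0.6 points (HR 0.4) and 0.9 (HR 0.6) under moderate effects, and 1.4 and 1.9 under strong effects (paired standard error 0.2 to 0.4). Type I error is 4.8% to 4.9%.

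**4. Chance imbalance.** For a factor present in 20% of 1500 patients, the standard error of the between-arm difference is √(4 × 0.2 × 0.8 / 1500) = 2.07 points. A difference of 3 points or more is 3/2.07 = 1.45 standard errors, a chance of about 15%. If the factor has HR 2, prevalences of 21.5% and 18.5% change the hazard ratio by a factor of 1.215/1.185 = 1.025. That is 0.025 on the log scale, about 8% of a standard error of 0.31. A 2-SD imbalance in prior stroke or age (HR 2.5, or 1.5 per SD) shifts the log HR by 0.04 to 0.05, about 0.15 standard errors. A p-value of 0.05 would then move to about 0.07 or 0.035.

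**The case against.** The strongest reply is that nothing here is an error. Adjusting for the factors used in randomization is a standard, prespecified choice, and type I error is held. This stands. A reader might infer from the omission that the primary analysis is biased or invalid. The documents do not support that: the confidence interval already allows for chance imbalance.

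A reader might also infer that substantial power is being given away. The planned effect is large ("LAA closure is expected to provide a 60% relative risk reduction"), and at HR 0.40 the gain under moderate assumptions lies between −0.5 and +0.6 points. Gains of 2 points or more appear only under strong assumed effects.

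Two statements about the plan would go too far. It does not call age a key stroke risk factor in its own right. Nor does it leave every listed risk factor unused, because OAC is on the list and is in the model. OAC also partly stands in for prior AF, which makes AF imbalance less likely than the 15% above, a figure that assumes simple randomization.

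Nor is the change quite free. Events per parameter fall. The plan's remedy for an adjustment covariate with non-proportional hazards is to stratify on it, which does not work for continuous age. The Gray's test p-value stays as it is.

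What remains is that prior stroke/TIA and age have no representation in the model, that prior AF has only a partial one, and that the loss of events per parameter caused no visible harm in the simulations.

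**Conclusion.** This is an optional improvement to a valid analysis. Adding age, prior stroke/TIA and prior AF gains about 0.5 to 1 power point under moderate prognostic effects and up to about 2 to 3 under strong ones, with simulated type I error of 4.3% to 4.9%. Simulation B, the smallest of the three, is also compatible with no gain under moderate effects. Protection against chance imbalance is real but minor at 1302 to 1500 patients. The figures depend on assumed prevalences and hazard ratios. That the covariates are collected and not used for adjustment, and that no other adjusted analysis is prespecified, can be read directly from the article.

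**What to change.** Before unblinding, add age (continuous), prior stroke/TIA (yes/no) and prior AF (yes/no) to the section Analyses of the primary outcome as fixed covariates of the cause-specific Cox model, next to site, surgery type and OAC. Under Sensitivity analyses, keep the model with the stratification factors only.

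Add a sentence on non-proportional hazards for age, for example an age-by-time term, or age bands used only for stratifying. State also that Gray's test remains unadjusted, so that the change bears only on the hazard ratio and its interval.

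If the sponsor prefers to keep the present primary model, prespecifying the larger model as a supportive analysis would still remove the post hoc problem, without the power gain.

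The cost is a few sentences in the SAP and three parameters. No new data are needed, since the items are already on the baseline list without the optional mark.
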